# A randomized controlled TRIal of cognitive BEhavioral therapy for high Catastrophizing in patients undergoing lumbar fusion surgery: the TRIBECA study

**DOI:** 10.1186/s12891-020-03826-w

**Published:** 2020-12-04

**Keywords:** Lumbar spinal fusion surgery, Pedicle screws, Pain catastrophizing, Cognitive behavioral therapy (CBT), Education, Chronic postsurgical pain (CPSP)

## Abstract

**Background:**

Around 20% of patients undergoing spinal fusion surgery have persistent back or leg pain despite surgery. Pain catastrophizing is the strongest psychological predictor for chronic postsurgical pain. Psychological variables are modifiable and could be target for intervention. However, randomized controlled trials evaluating the effectiveness of psychological interventions to reduce chronic pain and disability after spinal fusion in a population of patients with high preoperative pain catastrophizing scores are missing. The aim of our study is to examine whether an intervention targeting pain catastrophizing mitigates the risk of chronic postsurgical pain and disability. Our primary hypothesis is that targeted perioperative cognitive behavioral therapy decreases the risk of chronic postsurgical pain and disability after spinal fusion surgery in high catastrophizing patients.

**Methods:**

We will perform a two-center prospective, single-blind, randomized, controlled study comparing lumbar spinal fusion surgery outcome between 2 cohorts. Adult patients selected for lumbar spinal fusion with decompression surgery and a minimum score of 24 on the pain catastrophizing scale will be randomized with 1:1 allocation for either perioperative cognitive behavioral therapy (intervention group) or a perioperative education plus progressive exercise program (control group). Patients randomized to the intervention group will receive six individual sessions of cognitive behavioral therapy, two sessions before the operation and four after. Primary outcome is the Core Outcome Measures Index at 12 months. Secondary outcomes include pain, disability, depression and quality of life.

**Discussion:**

This is the first trial that evaluates the effectiveness of cognitive behavioral therapy as a perioperative tool to improve pain and disability after spinal fusion surgery in comparison with an educational/exercise control intervention, in patients with high levels of pain catastrophizing. If perioperative cognitive behavioral therapy proves to be effective, this might have important clinical implications, reducing the incidence of chronic postsurgical pain and improving outcome after spinal fusion surgery.

**Trial registration:**

Clinicaltrials (NCT03969602). Registered 31 May 2019,

## Background

The incidence of moderate to severe chronic postsurgical pain (CPSP) 12 months after surgery is around 12% in Europe, depending in part upon the surgical procedure [1]. World-wide, more than 230 million people undergo major surgery every year, and the global annual costs for new cases of CPSP are estimated to be hundreds of billions of dollars [2]. Emphasis on identifying the processes that underlie the transition to chronicity has been a neglected topic of investigation [3]. Perioperative protocols have historically not incorporated routine screening for patients at risk for CPSP or compromised function. However, early detection and management of these patients may modify the postsurgical pain trajectory and reduce the incidence of CPSP. Several predictive factors for CPSP have been identified, the most important being chronic preoperative pain, high intensity of acute postoperative pain and several psychological factors [4]. Of these psychological factors, pain catastrophizing has emerged as a robust predictor of pain severity and work disability among individuals with persistent musculoskeletal pain and is the strongest predictor for CPSP [5–7]. Catastrophizing is considered as a maladaptive coping strategy involving an exaggerated response to anticipated or actual pain. Individuals who catastrophize tend to ruminate about pain, magnify the threat value of pain and feel helpless when dealing with pain [5]. It is even postulated that catastrophizing could have a direct influence on the neurophysiologic mechanisms involved in pain processing [8].

CPSP and disability after spinal surgery poses a large problem. Around 20% of patients have persistent or recurrent pain in the back or limbs despite spinal surgery [9, 10]. Pain catastrophizing is associated with pain and disability in patients with lumbar spinal stenosis [11], and patients undergoing spine surgery with high catastrophizing scores are more likely to have higher maximum pain scores in the immediate postoperative period [12, 13]. This can have long term consequences, as previous studies have shown that high levels of pre-operative pain catastrophizing are associated with higher levels of pain and disability at 6 and 12 months after spine surgery [14–16].

Psychological variables are modifiable and could be a target for intervention. Patients who have participated in psychological interventions for chronic pain, including cognitive behavioral therapy (CBT) and acceptance and commitment therapy (ACT), report less pain, pain-related disability, and mood disturbance [17, 18].

Although psychological treatments delivered in the perioperative period have the potential to influence the trajectory of CPSP in patients undergoing spinal fusion [19], surgical patients have historically not been offered these interventions. Additionally, it has been argued that treating ‘high catastrophizers’ with CBT can result in 50% fewer patients developing CPSP within this group [20]. In almost all centers that perform spinal surgery for degenerative conditions, patient selection is based on medical and psychiatric comorbidities [21, 22]. Even though the so-called “yellow flags” are well known by surgeons, very few attempts have been made to address these factors or to identify categories of patients that could be at risk for CPSP. Well-designed randomized controlled trials (RCT) to determine the effectiveness of a CBT approach to reduce chronic pain and disability after spinal fusion in a population of patients with high preoperative pain catastrophizing scores are needed.

The aim of our study is to examine whether a perioperative intervention that targets pain catastrophizing can mitigate the risk of CPSP, i.e. improve the outcome of the surgical intervention, in patients that report high levels of pain catastrophizing and for whom lumbar spinal fusion surgery is indicated. We will start CBT already before surgery, to give patients the appropriate tools to manage symptoms during the immediate postoperative phase. The control group is offered an educational plus progressive exercise program (hereafter labelled ‘educational program’). We hypothesize that perioperative CBT, specifically designed to reduce pain catastrophizing, will improve outcome and decrease the risk of CPSP and disability after spinal fusion surgery, assessed by the Core Outcome Measures Index (COMI) questionnaire in high catastrophizing patients. Additionally, we will include a cohort of low catastrophizing patients receiving usual care to compare the outcome of spinal fusion surgery in low catastrophizing patients with high catastrophizing patients after perioperative CBT.

### Study design

This is a two-center prospective, single-blinded, randomized, controlled trial, in high pain catastrophizing patients with an indication for lumbar spinal fusion and decompression surgery, comparing two groups: one that receives perioperative CBT and one that receives the educational program. Figure 1 illustrates the study design, timing of pre- and postoperative sessions and follow-up evaluations. Estimated duration for the main investigational plan (e.g. from start of screening of first participant to last participant processed and finishing the study) is 4 years.

**Fig. 1 Fig1:**
[figure not shown]
Study design, timing of pre- and postoperative sessions and follow-up evaluations

### Ethical principles

Ethical approval has been granted by the Research Ethics Committee of the Canton Ticino, Switzerland (2018–00880 - CE 3361) and the Medical Ethical Committee Zuyderland, Heerlen, the Netherlands. Informed consent will be obtained in writing from all participants prior to study enrollment.

### Participants and recruitment

Adult patients who are undergoing surgery for a degenerative condition of the lumbar spine (lumbar spinal stenosis, spondylolisthesis or degenerative disc disease) using any kind of surgical decompression (laminectomy, hemilaminectomy, foraminotomy, with open or minimally invasive technique) associated with fusion, and able to read and speak Italian (site in southern Switzerland) or Dutch (site in the Netherlands) will be eligible for inclusion. One hundred and fifty patients will be enrolled at the outpatient clinic of the Department of Neurosurgery, Neurocenter of Southern Switzerland, Regional Hospital of Lugano, Lugano, Switzerland (Site 1) and the Department of Neurosurgery of Zuyderland Medical Center, Heerlen, The Netherlands (Site 2). All patients entering the screening phase will be registered on a Patient Registration Log and a unique registration number will be assigned. Clinical data will be assessed to evaluate a subject’s eligibility.

Patients will be excluded from the study if they meet any of the following criteria:
Plans to undergo major surgery within six months after current lumbar spinal fusion surgeryComorbid severe psychiatric conditions such as schizophrenia or personality disorderKnown or suspected non-compliance, drug or alcohol abuseInability to follow the procedures of the study, e.g. due to dementiaThe presence of any serious medical comorbidity such as sepsis or cancer that might cause disability or worsen the patient’s general health conditionPregnancyAn opioid intrathecal pumpPrisoners

Patients eligible for participation will be evaluated at least 6 weeks before surgery and asked for informed consent, and then to complete the PCS [23]. Patients with high pain catastrophizing, defined as a score of ≥24 on the PCS, will be eligible for randomization to perioperative treatment with CBT or educational program. This cut-off was initially based on a previous study in whiplash patients that showed that a pretreatment score of 24 or higher on the PCS best predicted follow-up pain ratings and work status after multidisciplinary treatment [24]. More recently, Tuna et al. [16] suggested an almost identical cut-off for the PCS (i.e. > 24) to obtain the highest sensitivity and specificity to predict unfavorable outcome after spine surgery, defined by as score on the Oswestry Disability Index (ODI) of 20 or higher.

A non-randomized group, consisting of low catastrophizing patients (score < 24 PCS), will be included as an observational cohort. These patients will not undergo any additional intervention besides usual care but will undergo the same data-collection as the high catastrophizing randomized groups.

### Randomization

A computer-generated randomization will be used to allocate the participant to either CBT or educational program with a 1:1 allocation. We will use block randomization stratified by center, with block sizes of 6. The randomization is performed by the Principal Investigator per site, who is not blinded for group assignment. The patients will be randomized immediately after they are included and have completed the PCS (one of the baseline assessments) to be able to make two pre-operative appointments with the patients in the intervention and control group.

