### Power considerations and statistical analysis

The primary outcome is the difference in the COMI between the study groups, 12 months after surgery. A difference of two points is considered clinically meaningful [44]. With an assumed SD of 2.5, the effect size of this difference, quantified as Cohen’s *d* is 0.80. Inclusion of 42 patients per intervention group will yield a power of 0.95 at a type-I error rate of 0.05. In addition, 42 patients with low pain catastrophizing scores will undergo the same assessments, but not receive any intervention besides care as usual. Taking into account a drop-out rate of 15%, 150 patients will be included in total.

Baseline patient characteristics will be stratified by group and presented as mean and standard deviation (SD), median and first and third quartile, and count and percentage, as appropriate. Differences in baseline characteristics between randomized groups will not be statistically tested, whereas differences with the separate control cohort will be tested using the independent-samples t-test for continuous variables, and Pearson’s chi-square test for categorical variables. In case of expected cell counts of less than 5, Fisher’s Exact test will be used instead.

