## Trial status

Participant recruitment started in February 2020 and is planned to continue until November 2022. An interim analysis is planned after 6 months follow up of 21 patients. It is expected that data regarding the intervention effects will be available at the end of 2023.

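### A single fixed block size of 6 per centre, with an unblinded site investigator performing the randomisation, makes on average a quarter of allocations deducible in advance

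*Protocol article*

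**What the plan says.** The Randomization section describes a computer-generated sequence used to "allocate the participant to either CBT or educational program with a 1:1 allocation". On its structure it says: "We will use block randomization stratified by center, with block sizes of 6". No second block size and no other stratification factor is given, so each site works through one sequence of 3:3 blocks.

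On who operates it: "The randomization is performed by the Principal Investigator per site, who is not blinded for group assignment". On timing: "The patients will be randomized immediately after they are included and have completed the PCS".

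The Study design section adds: "This is a two-center prospective, single-blinded, randomized, controlled trial". Under Trial status: "Participant recruitment started in February 2020 and is planned to continue until November 2022". The article is dated 4 December 2020, so the block size was public for most of the planned recruitment period.

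**The concern.** A fixed block whose size is known reveals its own ending. Once three patients in a block have gone to one arm, all remaining places belong to the other. Deducing this needs only the block size and the earlier assignments at that site. Here one unblinded person per site makes every assignment, and there is only one sequence per site to follow.

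Foreknowledge matters only if it can influence who is entered, or when. Participants and recruitment contains an exclusion that rests on judgement, namely suspicion that a patient will not comply. The Discussion names compliance with the intervention as the main limitation of the study. A patient thought unlikely to follow six sessions could be left out or deferred when the next place is CBT, without any bad intent. The two arms would then differ in motivation or expected adherence. Neither is in the primary model (baseline COMI and centre) or among the candidate covariates of the mixed model. The primary outcome is self-administered, and patients know which sessions they attend.

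**Working it through.** **Inputs.** From Randomization: block size 6, ratio 1:1, centre the only stratum, unblinded site investigator. From Power considerations and statistical analysis: 42 per group, 15% drop-out, 150 in total. The article gives no figure for predictability.

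**The plan's own figure first.** "With an assumed SD of 2.5, the effect size of this difference, quantified as Cohen’s *d* is 0.80". A two-sided t-test (sidedness is not stated, but two-sided reproduces the result) needs 41.6, so 42 per arm, and has power 0.952 at 42, against the stated 0.95. Drop-out: 42 / 0.85 = 49.4, so 50 per group; 3 × 50 = 150. The sample size reproduces and this point does not affect it. With three equal groups, two of them randomised, about 100 patients are randomised.

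**Allocations that are certain.** A 3:3 block has C(6,3) = 20 equally likely orders. Exactly k final places are forced when one arm receives its third patient at position 6 − k. There are 2 × C(5 − k, 2) such orders:

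- k = 1: 2 × C(4,2) = 12 orders
- k = 2: 2 × C(3,2) = 6 orders
- k = 3: 2 × C(2,2) = 2 orders

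Mean = (12 × 1 + 6 × 2 + 2 × 3) / 20 = 30 / 20 = 1.5 per block, and 1.5 / 6 = 25%. The closed form for a block of 2m agrees: 2m / (m + 1) = 6 / 4 = 1.5. The last place of every block is always forced.

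In patients: 0.25 × 100 = 25 randomised, or 0.25 × 84 = 21 of the 2 × 42 evaluable.

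**Allocations that can be guessed.** Suppose the tallier always guesses the arm that is behind and tosses a coin when the arms are level. Expected correct guesses per block are m + 2^(2m−1) / C(2m, m) − 1/2 = 3 + 32/20 − 0.5 = 4.1, and 4.1 / 6 = 68.3%, against 50% with no information.

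**What varying block sizes would change.** A simulation of 2,000 sequences of 42 patients assumed that the tallier knows the set of possible sizes but not the current one. The size sets are illustrative.

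| Block sizes | Allocations certain in advance |
|---|---|
| 6 only | 25% |
| 4 and 6 | about 6% |
| 4, 6 and 8 | about 2% |

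The guessing rate hardly moves. Every completed block is balanced, so the running difference between arms shows which arm is behind even when the block size is unknown. Expected correct guesses are 2 + 8/6 − 0.5 = 2.83 in a block of 4, 4.1 in a block of 6 and 4 + 128/70 − 0.5 = 5.33 in a block of 8. With the three sizes equally likely, the long-run rate is (2.83 + 4.1 + 5.33) / 18 = 68%. Varying the size removes certainty, not the tendency.

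**The case against.** The strongest reply is that the route from predictability to bias is partly blocked. Participants and recruitment puts every screened patient on a registration log with a unique number, so selective exclusion leaves a trace. Eligibility and consent come before the PCS, and only a patient-completed score of at least 24 leads to randomisation. When compliance is judged, it is therefore not yet known whether this patient will take the next place. Randomising immediately after inclusion and the PCS leaves little time for manipulation afterwards. These points stand and reduce the risk. They do not remove it, because the next arm can still be worked out before a patient is approached or scheduled.

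A list-concealment step in the full protocol, which is not shown, would not answer the point: hiding the next slot does not stop someone from counting past ones.

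A reader might also infer more than the article supports:

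- *That a quarter of allocations are known.* They are deducible on average, and only by someone who keeps a tally.
- *That the investigator selects patients or holds the list.* The article says that this person performs the randomisation. It does not say who judges eligibility, takes consent, or generates or keeps the sequence.
- *That the trial is otherwise open, with concealment as its main safeguard.* Outcome Measures states that those collecting outcomes are blinded to group and patients are blinded to the hypotheses. These measures act after allocation, so they do not prevent selection before it, but they are real.
- *That covariate adjustment cannot help.* It deals with selection through measured factors such as baseline COMI; selection on unmeasured ones remains.
- *That every outcome is self-reported.* Table 2 labels most outcomes so, but not medication usage.

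**Conclusion.** The point holds as a design weakness that should be corrected. Under the stated scheme, 25% of allocations are deducible with certainty on average (1 to 3 of 6 in any block) and 68% can be guessed. This is about 25 patients if about 100 are randomised. The result assumes that someone at the site keeps a tally and knows the block size. Both conditions are easily met when one unblinded person makes every assignment.

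These figures measure predictability, not bias. No effect on the COMI difference follows from them, and the article gives no sign of misuse. What is shown is an avoidable opportunity for selection on unmeasured factors, chiefly expected compliance.

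**What to change.** From the next block on in each centre, vary the block size at random, for example among 4, 6 and 8, and do not disclose the sizes to the sites. Release each allocation only after the patient has been irrevocably registered, through a system or an existing team member who takes no part in enrolment, such as the trial statistician. The second step matters because varying the size leaves the guessing rate near 68%: once registration is final, a patient cannot be withdrawn or deferred at the point of allocation. Keeping running tallies away from those who screen and schedule patients would reduce the remaining exposure.

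The cost is regenerating the remaining list and setting up the release step. If recruitment stops mid-block, the largest possible difference between arms within a centre rises from 3 to 4 patients. Sample size, eligibility, treatment and analysis are unchanged.

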### Comparators

#### Cognitive behavioral therapy

The CBT protocol was specifically developed for the present study by a team of psychologists with longstanding experience in the treatment of chronic pain patients. The intervention consists of six sessions, individually delivered by clinical video teleconferencing, and specifically aiming to reduce pain catastrophizing [25]. Two sessions are delivered before surgery (resp. at 3–6 weeks and 1–3 weeks pre-surgery) and four sessions after surgery. The four post-surgical session will start approximately 2 weeks after surgery, with sessions spaced one week apart (allowing a range of 2–3 weeks to prevent scheduling difficulties). All sessions have a duration of 60 min except for the first session that will take 90 min. Details of timing and the content of each sessions can be found in Table 1. In short, sessions focus on pain education, identifying, challenging and replacing catastrophizing thoughts, discussing fears of surgery, activities and goals after surgery, consequences of avoidance behavior, adaptive means for accomplishing interpersonal needs and relapse prevention. It also includes progressive muscle relaxation (PMR) training to provide patients with tools to cope with acute postoperative symptoms and to enhance their feelings of control. The protocol is manualized and the therapists delivering the treatment record after each session which components have been addressed. Patients receive a workbook consisting of a brief summary of the pain education, and for each session an explanation of the exercises for that week, several pages with forms to fill in and some examples. The homework is sent to the therapist before the start of the next session. Patients also receive an audio file with a recording of the PMR exercise that they are requested to practice at least once a day.

**Table 1 Tab1:** timing and content of cognitive behavioral therapy sessions

Timing	Aim	Content
Session 1 6–3 weeks pre-surgery 90 min	Building relationship Providing treatment rational Pain education Teaching relaxation	Gathering personal, medical and pain history Education on association between, cognitions, emotions, behavior and consequences Education on disconnection of “damage” or injury and perceived pain Building awareness of the impact of stress and fear on pain Explaining goals of the six sessions Practicing progressive muscle relaxation *Homework*: ABC belief monitoring (registering thoughts, emotions and consequences in pain situations) List “difficult” situations Practice progressive muscle relaxation
Session 2 3–1 weeks pre-surgery 60 min	Identifying catastrophizing thoughts Discussing fears of surgery	Homework review from previous session Introduction of the concept “catastrophizing” Identifying catastrophizing thoughts from homework Practicing with challenging and replacing catastrophizing and other maladaptive thoughts *Homework*: ABC belief monitoring (diary) Practice relaxation techniques
Session 3 1–3 weeks post-surgery 60 min	Challenging and replacing catastrophizing thoughts	Homework review Identify and replace catastrophizing thoughts Discussion of new fears and challenges *Homework*: ABC belief monitoring (diary) Practice relaxation techniques
Session 4 2–5 weeks post-surgery 60 min	Challenging and replacing catastrophizing thoughts Overcoming avoidance Learning new ways of coping	Homework review Discuss to which maladaptive behavior catastrophizing might lead Discuss how to attain goals in an alternative way Identify barriers for adaptive coping Discuss how to deal with upcoming stressful situations *Homework*: ABC belief monitoring (diary) Identify needs being met by avoidance behavior and list alternative options for attaining those needs Practice relaxation techniques
Session 5 3–6 weeks post-surgery 60 min	Learning more adaptive means for accomplishing interpersonal needs	Homework review Note and discuss progress Continue with challenging and replacing catastrophizing thoughts Discuss challenges from previous week Focus on how to communicate needs to environment and identify barriers in doing so. *Homework*: ABC belief monitoring (diary) Practice relaxation techniques
Session 6 4–8 weeks post-surgery 60 min	Maintenance Promoting continued practice	Discussing challenging catastrophizing thoughts as a longterm project Reviewing and summarizing the most important concepts Patients receive the completed homework binder

Each patient will be treated by a single therapist. At the Swiss site, CBT will be delivered by one of the clinical psychologists who was involved in developing the protocol. At the Dutch site, CBT will be delivered by one of two clinical psychologists. Both have prior experience in pain management and are additionally trained in working with the current protocol by one of the psychologists involved in its development. All CBT providers have to follow the guideline that was created for this study, to assure that all sessions will be held in the same way. All patients in the CBT group will receive a workbook with pages to fill out for every session and with some additional exercises.

